#### Other measures

Sociodemographic information will be collected during screening and at all-time points. Data will be collected on demographics (e.g., gender, age, religion), education (e.g., GPA, year of study, field of study), and living conditions (e.g., housing, living allowance). Contamination questions will be asked at the one-week post-test and the three-month follow-up in both arms. For the intervention group, participants will be asked, ‘Did you discuss SH + with others?’ For the control group, participants will be asked, ‘Did you know about SH+?’ if the answer is ‘yes’, there will be several follow-up questions (e.g., ‘How did you know about SH+’, ‘Did you learn about the SH + such as reading the book or listening to the audio?’).

*Translation and adaptation of the study measures*. PSYCHLOPS, MIMIS, and CSRI were not yet available in Bahasa Indonesia. Therefore, in this project, we adapted these three instruments. In general, the adaptation process included translation, synthesis, back-translation, and final synthesis. The Indonesian research team (DA and [name]) carried out the synthesis part, while hired professionals’ translators did the translation into Bahasa Indonesia and back-translation into English (different translator).

In the adaptation of PSYCHLOPS, there were no changes between the English version and the Bahasa Indonesia version. For the adaptation of MIMIS, we used the result of a qualitative interview with university students (*N* = 30) in Indonesia about their problems. The results of these interviews informed new items related to daily challenges reported by university students in Indonesia, resulting in a version of the MIMIS adapted for Indonesian university students. We adapted the CSRI based on the health system in Indonesia and had a consultation with an expert in health economics.

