#### Contamination

To minimize the risk of contamination, we implemented several measures: During the first session, participants in the SH + group are explicitly asked not to share or discuss the intervention materials with others outside the SH + group. We do not explicitly restrict the control group from independently accessing the SH + materials on the WHO website. Therefore, to know if they were accessing the material, during the T2 and T3 we ask them about whether they knew about the SH+ (see other measures above).

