#### Data analysis

Data will be analysed once all data has been collected; no interim analyses will be performed. However, participants can withdraw from the study or the session anytime without giving a reason.

**Quantitative data (RCT).** An intention-to-treat (ITT) approach will be used to conduct data analysis both in primary and secondary outcomes, and the unit of the analysis is individual. The primary analysis will simultaneously assess the treatment effect on the mean PHQ-ADS total score at each time point. All participants randomized to either group will be analysed, regardless of whether they complete the intervention. The ITT population will consist of all participants randomized to the competing intervention strategies who have at least baseline assessment data available. The main conclusion of the trial will be based on the ITT analysis of the primary outcome (i.e., the effect on the PHQ-ADS score at the three-month follow-up).

Adherence will be defined based on attendance at least three sessions of SH+. A per protocol (PP) approach will be used to test the robustness of the intervention results for all outcomes, which will include only SH+/ECAU participants who attend at least three sessions of the SH + intervention [24]. The attendance of the participants will be recorded by the facilitator(s) of the SH+.

Linear mixed models will be used for the PHQ-ADS (primary outcome) and secondary outcomes to evaluate the treatment effect on all endpoints at t2, t3 and t4, with time as a fixed effect, baseline PHQ-ADS score as a covariate and participants as random effects. A t-test will be used to analyse the differences between the two study arms. Multiple imputation will be used to handle the missing values at 3 months. A sensitivity analysis will be conducted to compare the full sample with the sample that excludes ECAU participants who indicated being exposed to SH + materials.

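### The per-protocol and contamination analyses each select on post-randomisation behaviour in one arm only, so they are open to selection bias, and per-protocol agreement with ITT cannot show robustness

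*Protocol article*

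**What the plan says.** All of the following is in the protocol article.

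- **Main inference (Data analysis).** "The main conclusion of the trial will be based on the ITT analysis of the primary outcome", at three months. Everyone randomised with baseline data is analysed, whether or not they complete the intervention. The mixed model carries baseline PHQ-ADS as a covariate.
- **Per-protocol analysis (Data analysis).** Its stated purpose: "A per protocol (PP) approach will be used to test the robustness of the intervention results for all outcomes". Its population is one "which will include only SH+/ECAU participants who attend at least three sessions of the SH + intervention". No rule is given for how ECAU participants enter it.
- **Contamination analysis (Data analysis).** A sensitivity analysis is to "compare the full sample with the sample that excludes ECAU participants who indicated being exposed to SH + materials".
- **How exposure arises (Contamination).** "We do not explicitly restrict the control group from independently accessing the SH + materials on the WHO website".
- **How exposure is measured (Other measures).** "Contamination questions will be asked at the one-week post-test and the three-month follow-up in both arms". Controls are first asked whether they knew about SH+. Those who say yes get follow-up questions, including whether they used the book or audio.
- **Attrition (Sample size).** The plan allows for 50%.

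**The concern.** Both analysis sets are defined by what people do after randomisation, and each rule can act in one arm only. Students who come to three or more sessions may differ in motivation, distress or free time from those who do not. Their ECAU counterparts, the students who would have attended if offered SH+, cannot be picked out, so nobody comparable is removed from ECAU. The contamination rule has the same defect in the other arm: controls who look for the materials chose to do so, and no matching group is removed from SH+.

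Interpretation is at stake. If PP agrees with ITT, the plan's wording invites the reader to take that as confirmation, for every outcome. But PP can agree or disagree with ITT through selection alone. In the contamination analysis, any change in the estimate mixes two things: removal of true contamination, and a change in the prognosis of the remaining controls. Neither analysis answers the useful question of what SH+ does in those who take it up.

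**Working it through.** The plan gives no figure for this point, so there is none to reproduce. The check has two parts.

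**1. Who is removed, and from which arm**

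| Analysis | Removed from SH+ | Removed from ECAU | Known when |
|---|---|---|---|
| ITT | nobody for non-completion | nobody for non-completion | – |
| PP | attenders of fewer than three sessions | no rule stated | during the five weeks of sessions |
| Contamination | nobody | those reporting exposure | t2 and t3 |

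Read literally, the PP rule leaves no comparator. The workable reading is attenders against all ECAU participants, but that is an inference.

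In the contamination analysis, controls who do not answer at t2 or t3 cannot report exposure and so stay in. With 50% attrition planned for, this could be a large group. The planned multiple imputation is described for missing values at three months; exposure status is not mentioned. The opening question asks about knowing of SH+, while the Discussion says both groups were informed about the intervention. Awareness alone therefore cannot mark exposure.

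**2. How large the shift could be**

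The documents give no attendance rate, exposure rate or prognostic correlation, so these are assumptions. Let untreated outcome have SD 1. Let attendance or exposure follow a normal propensity with correlation r to better untreated prognosis, let φ be the standard normal density, and let there be no treatment effect.

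*PP, proportion p attending:* shift = r × φ(z)/p, where z cuts off an upper tail of p.

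For p = 0.6: z = −0.253, φ(z) = 0.386, and φ(z)/p = 0.644.

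- r = 0: 0
- r = 0.1: 0.064 SD towards SH+
- r = 0.2: 0.129 SD
- r = 0.3: 0.193 SD
- negative r: same size, against SH+

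A simulation with 2,000,000 draws per arm at other attendance rates behaves the same way:

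| Attending | r = 0 | r = 0.1 | r = 0.3 |
|---|---|---|---|
| 50% | 0 | 0.08 | 0.24 |
| 70% | 0 | 0.05 | 0.15 |
| 90% | 0 | 0.02 | 0.06 |

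*Contamination, proportion q of ECAU excluded:* shift = r × φ(z)/(1 − q), where z cuts off an upper tail of q. With r = 0.2:

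- q = 0.10: 0.2 × 0.1755/0.9 = 0.039 SD
- q = 0.20: 0.2 × 0.280/0.8 = 0.070 SD

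This favours SH+ if controls with better prognosis seek the material, and works against it if the more distressed do.

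All these figures are before adjustment. Baseline PHQ-ADS in the model would remove the part of the selection that it explains, and no more.

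**The case against.** The case for leaving the plan alone has real force.

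- **The trial's conclusion is protected.** It rests on ITT, and both analyses are supplementary. A reader might infer that the primary result is compromised; nothing in the document supports that. This stands in full.
- **Bias is possible, not shown.** It is tempting to say that both analyses are biased. That would need attendance or exposure to be related to prognosis beyond baseline PHQ-ADS, and the document has no data on this. More distressed students may attend more, which would reverse the sign. This stands.
- **The robustness claim is made for PP only.** The contamination check is called a sensitivity analysis and is set beside the full sample, so the unselected result remains visible. This stands.
- **The shift cannot safely be scaled to the planned effect.** A reader might divide 0.064 and 0.193 by 0.3 and get about 21% and 64%. The Sample size section does not name the metric of its 0.3. Its N = 148 is reproduced as Cohen's f = 0.3 at a single measurement (power 0.952), whereas a standardised difference of 0.3 would need 578 in a two-sided comparison at one time point. For two equal groups f = 0.3 corresponds to d = 0.6, and the shares fall to about 11% and 32%. No percentage should be quoted as a finding.
- **CACE is no clean substitute.** SH+ participants are given the book, and some will attend one or two sessions. Counting them as untreated strains the exclusion restriction and may inflate the estimate. Reading or listening by a control is not the same treatment as guided group sessions. Replacing both planned analyses would therefore go too far.
- **An analysis plan may hold the detail.** That covers unstated methods. It does not cover what the article itself fixes: the one-arm PP rule and the purpose assigned to it.

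**Conclusion.** The point holds as a limited one about supplementary analyses. The PP set restricts only SH+ and the contamination set restricts only ECAU, each by post-randomisation behaviour. Both are open to selection bias of unknown size and direction, and PP agreement with ITT is not evidence of robustness. Under assumed 60% attendance and a prognostic correlation of 0.1 to 0.3, the PP shift is 0.06 to 0.19 SD before baseline adjustment; it is zero with no correlation and reversed with a negative one. The figures assume a normal propensity and all ECAU participants as comparator. They illustrate what could happen and do not estimate what will. The change is a cheap improvement and is not needed to protect the main result.

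**What to change.** 1. Keep PP, name all ECAU participants as its comparator, and label it descriptive and non-randomised. Remove the wording that it tests robustness.
2. Keep the contamination exclusion with the same label. Define exposure as use of the SH+ book or audio, not awareness, and say how controls with no t2 or t3 answer are handled.
3. Add a supplementary CACE estimate on the multiply imputed ITT set, with randomised arm as instrument, adjusted for baseline PHQ-ADS, and attendance at three or more sessions as treatment received.
4. Add two sensitivity versions of it: one counting any attendance as treated, because book receipt and partial attendance strain the exclusion restriction; and one counting ECAU use of the book or audio as exposure, with missing exposure imputed.

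**Cost.** No new data: facilitators already record attendance and the exposure questions are already planned. The extra work is modest, the imputation of exposure being the larger part. The CACE needs the exclusion restriction and monotonicity, and its interval is wider. Roughly, the ITT effect and its standard error are divided by the difference in uptake between arms. With an assumed 60% uptake in SH+ and none in ECAU, the interval is 1/0.6 = 1.67 times as wide as for ITT; with 10% uptake in ECAU it is 1/(0.6 − 0.1) = 2 times as wide.

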**Methods:**

The SH + intervention will be tested in a pragmatic superior randomized controlled trial (RCT) with two parallel arms. SH + will be tested among Indonesian university students with symptoms of psychological distress (Patient Health Questionnaire-9; PHQ-9 ≥ 5.5 < 20). The participants (*n* = 296) will be randomized into either the intervention group that receives SH + with enhanced care as usual (ECAU), or into the ECAU only with a 1:1 allocation ratio. The primary outcome is the reduction in psychological distress assessed with the Patient Health Questionnaire Anxiety and Depression Scale (PHQ-ADS) at three-month follow-up. The secondary outcomes are symptoms of depression, anxiety, perceived stress, functioning, resilience, quality of life, identified problems, treatment acceptability, and cost-effectiveness.

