#### Assessment

Data will be collected through self-report assessments at four times points: *t*_*1*_ (baseline – sent at least 10 days before the SH + to the participants already enrolled), *t*_*2*_ (post-SH+, week-7), *t*_*3*_ (main time point – 3 months after SH+), and *t*_*4*_ (follow-up – 6 months after SH+) with the Castor Electronic Data Capture (EDC) software program [33]. Each assessment will be provided via e-mail with a link to the self-report questionnaire to each participant and can be completed on any device with internet access. The time to complete each assessment is approximately 20–30 min. If an assessment remains incomplete, the participant will receive a maximum of three reminders on days 3, 7, and 10 through various communication channels to encourage retention. The participants will receive IDR 50,000 e-money for each completed assessment, with a maximum of four e-money awards (*t*_*1*_ to *t*_*4*_).

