#### Primary outcome measure

The primary outcome and end point will be the reduction in psychological distress as measured by the total score on the Patient Health Questionnaire Anxiety and Depression Scale (PHQ-ADS) [35, 36] at three-month follow-up. The PHQ-ADS is the validated combined sum score of the Patient Health Questionnaire (PHQ-9) [29] and the Generalized Anxiety Disorder (GAD-7) questionnaires [37]. Psychological distress, as measured by the PHQ-ADS, will also be collected at one-week and six-month follow-up.

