#### Secondary outcome measure

All secondary measurements will be collected at one week, three months, and six months post-treatment. Depression symptoms are measured using the PHQ-9 [29]. The PHQ-9 is a self-administered questionnaire consisting of nine items that can be scored from 0 (not at all) to 3 (almost every day), with a total score ranging from 0 to 27. The PHQ-9 has been validated in Bahasa Indonesia demonstrating good internal consistency (Cronbach’s alpha of 0.885), and a cut-off score of 5.5, which indicates that people have symptoms of depression [38].

Anxiety symptoms are measured using the GAD-7 [37]. It consists of seven items with response options ranging from 0 (not at all) to 3 (almost every day), with a total score ranging from 0 to 21. The GAD-7 was translated into Bahasa Indonesia and validated with a Cronbach’s alpha 0.867 and a cut-off score of 6 [39].

The Perceived Stress Scale (PSS) will be used to measure perceived stress. The PSS is a measure of an individual’s perception of recent stress [40]. The items are designed to measure how unpredictable, uncontrollable and overwhelming respondents feel their lives are. The questions in the PSS ask about feelings and thoughts over the past month. The PSS consists of 10 items that are scored from 0 to 4 with the response options being ‘*never*’, ‘*almost never*’, ‘*sometimes*’, ‘*fairly often*’ and ‘*very often*’. The PSS in Bahasa Indonesia showed very good item reliability (0.98) and person reliability (0.79) [41].

General functioning will be measured by the WHO Disability Assessment Schedule 2.0 (WHODAS 2.0) -12 items [42]. The WHODAS 2.0 is a generic assessment tool that can be used to measure health and disability at the population level or in clinical practice. It consists of 12 items that assess six activity domains: understanding and communicating, getting around, self-care, getting along with people, life activities and participation in society. For each item, the participants indicate the level of difficulty (none, mild, moderate, severe, extreme). The Bahasa Indonesia version of WHODAS 2.0–12 items showed good internal consistency (Cronbach’s alpha between 0.634 and 0.853) and test-retest reliability (0.764 and 0.866) [43].

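### The mixed model adjusts the secondary scales for baseline PHQ-ADS only, although their own t1 values are collected; for scales outside PHQ-ADS this costs precision and only partly corrects chance imbalance

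*Protocol article*

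**What the plan says.** The Data analysis section gives a single model specification: "Linear mixed models will be used for the PHQ-ADS (primary outcome) and secondary outcomes to evaluate the treatment effect on all endpoints". It applies to t2, t3 and t4, and its terms are set out in the same sentence: "with time as a fixed effect, baseline PHQ-ADS score as a covariate and participants as random effects". The primary and secondary outcomes and the covariate thus stand together. No other sentence gives a secondary scale its own baseline. The t-test mentioned next names no covariate. Because only t2, t3 and t4 are modelled, the t1 values do not enter as responses either.

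The abstract lists the outcomes concerned: "The secondary outcomes are symptoms of depression, anxiety, perceived stress, functioning, resilience, quality of life, identified problems, treatment acceptability, and cost-effectiveness". The Secondary outcome measure section mentions only the later measurements ("All secondary measurements will be collected at one week, three months, and six months post-treatment"), but Table 1 marks PHQ-9, GAD-7, PSS, WHODAS 2.0, EQ-5D-5L, MIMIS, PSYCHLOPS and CSRI at baseline as well, in a column placed before randomization. The Assessment section describes t1 as "baseline – sent at least 10 days before the SH + to the participants already enrolled".

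PHQ-ADS is defined under Primary outcome measure as the sum of PHQ-9 and GAD-7. Cost and QALY differences have their own generalized linear regression.

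**The concern.** In a randomized comparison, the baseline value of the outcome itself is usually the strongest available predictor of its follow-up value. PHQ-ADS contains depression and anxiety items. It does not directly measure perceived stress, functioning, quality of life or self-identified problems, so it is likely to be a weaker predictor for those scales.

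Two things are at stake. First, the secondary effects are estimated with wider intervals than the collected data allow. Second, if the arms differ by chance on, say, baseline PSS, adjusting for PHQ-ADS removes only the part of that difference that the two scales share. The Goals and hypotheses section predicts superiority on these outcomes, so their estimates will be read as tests of stated hypotheses. The Randomization section describes blocked 1:1 allocation and names no stratification factor that would balance the secondary baselines.

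**Working it through.** The plan states no figure on this point, so there is none to reproduce. The check is how much is lost by using baseline PHQ-ADS in place of the own baseline.

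**Inputs from the article (Sample size).** 296 randomized, 148 per arm, 50% attrition. Completers: 296 × 0.5 = 148, or 74 per arm.

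**Assumed inputs (the article gives no correlations).** r_own, the correlation of follow-up with own baseline: 0.5 to 0.6. r_x, the correlation of follow-up with baseline PHQ-ADS: 0.3 to 0.4. It is also assumed that baseline PHQ-ADS predicts follow-up only through the own baseline, so that r_x = c × r_own, where c is the correlation between the two baselines. Hence c = r_x / r_own.

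**Precision.** Residual variance after adjustment is proportional to 1 − r². The variance ratio, PHQ-ADS adjustment against own-baseline adjustment, is (1 − r_x²)/(1 − r_own²), and the SE ratio is its square root. Equivalent completers are 148 divided by the variance ratio.

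**Chance imbalance.** One standard error of a baseline difference at 74 per arm is √(2/74) = 0.164 SD. With PHQ-ADS adjustment, an own-baseline imbalance d leaves on average d × r_own × (1 − c²) in the estimate.

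| r_own | r_x | c | Variance ratio | SE increase | Equivalent completers | Left in estimate (SD) |
|---|---|---|---|---|---|---|
| 0.5 | 0.4 | 0.80 | 0.84/0.75 = 1.12 | 6% | 132 | 0.164 × 0.5 × 0.36 = 0.03 |
| 0.5 | 0.3 | 0.60 | 0.91/0.75 = 1.21 | 10% | 122 | 0.164 × 0.5 × 0.64 = 0.05 |
| 0.6 | 0.4 | 0.67 | 0.84/0.64 = 1.31 | 15% | 113 | 0.164 × 0.6 × 0.56 = 0.05 |
| 0.6 | 0.3 | 0.50 | 0.91/0.64 = 1.42 | 19% | 104 | 0.164 × 0.6 × 0.75 = 0.07 |

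With no baseline adjustment at all, the same imbalance would leave 0.164 × 0.5 = 0.08 to 0.164 × 0.6 = 0.10 SD. PHQ-ADS adjustment therefore helps, but only in part.

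**Power at the unfavourable end.** For a 0.4 SD difference with 74 per arm, r_own = 0.6 and c = 0.5, power is 0.86 with own-baseline adjustment and 0.72 with PHQ-ADS adjustment.

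**Scales closely tied to PHQ-ADS.** Taking c = 0.9 as an illustration for PHQ-9 and GAD-7, the SE increase is 3.1% at r_own = 0.5 and 5.2% at r_own = 0.6. The 0.4 SD power at r_own = 0.6 is 0.82 against 0.86. A 0.164 SD imbalance leaves 0.164 × 0.6 × 0.19 = 0.02 SD.

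**If all 148 per arm contribute.** The standard error of a baseline difference falls to √(2/148) = 0.116 SD, and the amount left becomes 0.116 × 0.5 × 0.36 = 0.02 to 0.116 × 0.6 × 0.75 = 0.05 SD. The variance ratios do not change.

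**The case against.** The strongest reply is about reading. One condensed sentence in a journal article covers many outcomes, and baseline PHQ-ADS may have been meant only for the primary outcome, or as an example of adjusting for the baseline score. Covariates for secondary models are often left to an analysis plan. That intention is possible, but it is not what the sentence says: it names the secondary outcomes and "baseline PHQ-ADS score as a covariate" together. The covariate has been specified rather than left open, so a later plan would have to depart from the article to correct it.

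The reply stands on scope and size, where stronger readings are tempting:

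- A reader might infer that every secondary outcome is affected. Acceptability has no t1 measure in Table 1, and costs and QALYs have a separate regression. Resilience is defined by linking changes in mental health to stressor exposure, so baseline MIMIS is an own baseline only where MIMIS is analysed as a score.
- A reader might infer that baseline imbalance goes uncorrected. For PHQ-9 and GAD-7 it is largely corrected, because they make up PHQ-ADS. For the other scales it is corrected as far as they correlate with PHQ-ADS.
- A reader might take 0.08 SD or more as the carry-over from a one-standard-error imbalance. That is the figure with no adjustment at all.
- The figure of 74 per arm counts completers. The plan is intention-to-treat with multiple imputation at three months, so the effective number may be larger.

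**Conclusion.** The point holds for the scale outcomes in the mixed model that are not components of PHQ-ADS: PSS, WHODAS 2.0, EQ-5D-5L, PSYCHLOPS, and MIMIS where analysed as a score. Followed as written, the plan gives them a residual variance about 12 to 42% larger than own-baseline adjustment would (SE about 6 to 19% larger), and a one-standard-error imbalance at 74 completers per arm leaves roughly 0.03 to 0.07 SD in the estimate. These sizes rest on assumed correlations. They shrink when the scale tracks PHQ-ADS closely, as PHQ-9 and GAD-7 will, and grow when own-baseline correlations are higher than assumed.

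The documents do not support a claim of systematic bias. Randomization keeps the estimates unbiased on average, and the cost is lost precision plus error conditional on a chance imbalance. Nor is the main conclusion in question: it rests on PHQ-ADS at three months, for which baseline PHQ-ADS is the right covariate. This is a worthwhile correction to the secondary analyses, and no more than that.

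**What to change.** In the Data analysis section, replace the covariate by *the baseline (t1) value of the outcome being analysed* for every scale outcome in the mixed model: baseline PHQ-ADS for PHQ-ADS, PSS for PSS, WHODAS 2.0 for WHODAS 2.0, and likewise for PHQ-9, GAD-7, EQ-5D-5L, PSYCHLOPS and any MIMIS score. Baseline PHQ-ADS may stay as an additional covariate for the secondary scales. If the present wording was meant for the primary outcome only, say so and add the rule for the others.

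The cost is one phrase. Table 1 already schedules every measurement needed, so participants carry no extra burden. The article plans no interim analysis and analyses the data only once collection is complete, so the change can be fixed in writing before any outcome data are examined.

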### Analysis

#### Sample size

By utilizing G*Power [55], considering psychological distress as the primary outcome with an effect size of 0.3, a power calculation for a repeated measures design suggests a minimum sample size of *N* = 148 (power = 0.95, α = 0.05, rho = 0.9) to detect the expected effect size. Accounting for a 50% attrition rate observed during our pilot, a total of 296 participants will be recruited (148 participants in each arm). At each university, there is an intervention group and a control group. Each group will consist of 20–30 participants.

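### The arm comparison at three months is described by two methods, a mixed model and an unranked t-test, and neither is named as the source of the primary result

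*Protocol article*

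**What the plan says.** All the relevant text is in the Data analysis section of the protocol article.

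- **Primary analysis:** "The primary analysis will simultaneously assess the treatment effect on the mean PHQ-ADS total score at each time point".
- **Basis of the conclusion:** "The main conclusion of the trial will be based on the ITT analysis of the primary outcome", which the section identifies as the PHQ-ADS effect at the three-month follow-up. No method is named in that sentence.
- **Model:** linear mixed models are to be used for the primary and secondary outcomes "to evaluate the treatment effect on all endpoints at t2, t3 and t4", and are specified "with time as a fixed effect, baseline PHQ-ADS score as a covariate and participants as random effects". Neither arm nor arm-by-time is in the list.
- **Second method:** "A t-test will be used to analyse the differences between the two study arms". No outcome, time point, covariate or rank is attached, and no other section gives the test a role.
- **Missing data:** "Multiple imputation will be used to handle the missing values at 3 months". The section does not say whether the imputed data go into the mixed model, the t-test or both.

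**The concern.** The trial's conclusion depends on one number, the arm difference in PHQ-ADS at three months, and the text offers two ways to obtain it. The model is written without the terms that carry the treatment effect, and the sentence that does speak of comparing the arms hands that job to a t-test. A statistician working from this text could take the primary p-value from the model's t3 contrast or from the t-test and say, in either case, that the protocol was followed.

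Two things are at stake. The first is precision: a two-sample t-test discards the baseline PHQ-ADS score, which the model uses. The second is error control: if the choice between methods is still open when the results are seen, there are two chances to reach significance on one endpoint.

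**Working it through.** **1. Does the text itself settle which method is primary?** The primary analysis is said to assess the effect simultaneously at each time point. A longitudinal model with arm and arm-by-time does that; a two-sample t-test does not. The mixed-model sentence also names PHQ-ADS as the primary outcome, while the t-test sentence names no outcome. So the text leans towards the model. It never says that the three-month conclusion comes from the model, and it never makes the t-test secondary.

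**2. Does the sample size settle it?** Inputs from Sample size: effect size 0.3 ("considering psychological distress as the primary outcome with an effect size of 0.3") and "power = 0.95, α = 0.05, rho = 0.9". Two-sided testing is assumed, as the text does not state sidedness.

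Formula: noncentral F for a two-group between-subject effect over m measurements, with λ = N·f²·m / (1 + (m − 1)·rho).

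| Reading of 0.3 | m | Total N for 95% power |
|---|---|---|
| f = 0.3 | 1 (rho drops out) | 148 (power 0.952) |
| f = 0.3, rho = 0.9 | 2 | 140 |
| f = 0.3, rho = 0.9 | 3 | 138 |
| f = 0.3, rho = 0.9 | 4 | 136 |

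The stated 148 is reproduced exactly with a single measurement, which is an unadjusted two-arm comparison with 74 per arm at d = 2 × 0.3 = 0.6. The attrition step also reproduces: 148 / (1 − 0.5) = 296. The section nonetheless describes a repeated-measures calculation. It therefore does not show which analysis was meant to carry the conclusion.

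**3. How far apart are the two methods in precision?** Let r be the correlation between baseline and three-month PHQ-ADS. Baseline adjustment multiplies the standard error of the arm difference by √(1 − r²), so the t-test's standard error relative to the adjusted one is 1/√(1 − r²). The protocol gives no value for r. Its rho of 0.9 is a power-calculation input for repeated measures; using it as the baseline-to-follow-up correlation is an assumption, so it serves as the top of a range.

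| r (assumed) | √(1 − r²) | SE ratio, t-test / adjusted |
|---|---|---|
| 0.5 | √0.75 = 0.866 | 1.15 |
| 0.7 | √0.51 = 0.714 | 1.40 |
| 0.9 | √0.19 = 0.436 | 2.29 |

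Power with 74 analysed per arm and one follow-up visit, two-sided 5%:

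| True effect | t-test | Adjusted, r = 0.5 | r = 0.7 | r = 0.9 |
|---|---|---|---|---|
| d = 0.3 | 0.44 | 0.55 | 0.72 | 0.99 |
| d = 0.6 | 0.952 | 0.987 | 0.999 | above 0.999 |

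Both effects are shown because the protocol does not say whether its 0.3 is d or f.

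**4. What would it cost to leave the choice open?** Under no effect, the adjusted and unadjusted test statistics are approximately bivariate normal with correlation √(1 − r²). The chance that at least one exceeds 1.96 in absolute value is:

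| r (assumed) | Correlation of the two statistics | P(either significant) |
|---|---|---|
| 0.5 | 0.866 | 7.3% |
| 0.7 | 0.714 | 8.3% |
| 0.9 | 0.436 | 9.2% |

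**The case against.** The strongest reply is that this is a journal article and that its stated purpose fills the gap. A model meant to give the treatment effect at t2, t3 and t4 must contain arm and arm-by-time, and an article may abbreviate a term list. That stands. A reader might infer that the planned model cannot estimate a treatment effect, or that it would report one effect averaged over the three visits. The stated aim of an effect at each time point supports neither reading.

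A reader might also infer that the t-test would use only participants observed at three months. The text does not support that: imputation at three months is planned in the very next sentence, and the section says all randomized participants will be analysed.

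That the test is unadjusted is an inference too. It is the plain reading of a t-test between two arms, but a t-test of the model's arm contrast is possible.

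Finally, nothing in the protocol permits the team to claim whichever test succeeds. The 7% to 9% is the cost if the choice stays open, not a feature of the written plan. The standard-error ratios compare a single-visit adjusted analysis with a t-test, so they only approximate the longitudinal model.

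None of this gives the t-test a role. Abbreviation explains missing terms; it does not explain a second method stated for the same comparison.

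**Conclusion.** The point holds as a fault of specification. The endpoint (PHQ-ADS at three months) and the population (ITT) are fixed, and the text leans towards the mixed model. But the arm comparison is also assigned to a t-test that has no rank and does not fit the article's own description of the primary analysis. The missing arm and arm-by-time terms are a drafting omission that adds to the ambiguity.

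The size depends on r, which the protocol does not give. Over r from 0.5 to 0.9, the t-test's standard error is 1.15 to 2.29 times the adjusted one, and the type I error is 7.3% to 9.2% if either result could be claimed. These figures assume a two-sample test without baseline adjustment, two-sided testing at 5% and one follow-up visit.

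**What to change.** Amend the Data analysis section as follows:

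- List arm, time (categorical), arm-by-time and baseline PHQ-ADS as fixed effects, with a participant random effect.
- Name the model-based arm contrast at t3, with its 95% CI, as the single primary result. The contrasts at t2 and t4 are secondary.
- Delete the t-test sentence, or label the test secondary or descriptive and state its outcome and visit.
- State which analysis the multiple imputation at three months feeds.

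No further model terms are needed to resolve this point. The cost is a few sentences, with no change to recruitment, data collection or sample size. Because the protocol plans no interim analyses and will analyse only once all data are in, the change can be made before any comparison between arms is seen, and it should be dated accordingly.
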